#### 11.6.4 Storage Conditions

Letrozole must be stored, handled and dispensed as detailed in the current Summary of Product Characteristics (SmPC) of the brand being used.

#### 11.6.5 Returns and destructions

All previously dispensed, unused Letrozole should be destroyed once the amount of remaining tablets has been counted and recorded in the relevant accountability forms. Refer to the pharmacy manual.

#### 11.6.6 Adverse Events

The most common Adverse Events (AEs): Vascular disorders, flushing, cerebrovascular accident, hypertension, thromboembolic event, angina, skin rash, increased sweating, increased hepatic enzymes and arthralgia/arthritis.

See package insert for complete list of adverse effects and the current SmPC for the brand being used.

[figure not shown]

### **11.6.7 Contraindications**

Avoid co-administration of Letrozole with tamoxifen, other anti-oestrogens or oestrogen-containing therapies as these substances may diminish the pharmacological action of Letrozole

## **11.7 Megestrol acetate 40mg tablets**

### **11.7.1 Legal status**

Megestrol acetate 40mg is not licenced in the UK but is available in the USA. This trial is being carried out under a CTA. Megestrol 40mg is therefore only to be used by the named Investigators, for the patients specified in this protocol, within the trial.

Description: Megestrol acetate is a potent progestogen that exerts significant anti-oestrogenic effects. It has no androgenic or oestrogenic properties. It has anti-gonadotropic, anti-uterotropic and anti-androgenic/anti-myotropic actions. It has a slight but significant glucocorticoid effect and a very slight mineralocorticoid effect.

Supply: Megestrol 40mg will be supplied free of charge to participating sites. Megestrol 40mg will be labelled and distributed by Mawdsley-Brooks & Co Ltd in accordance with local regulations and Good Manufacturing Practice.

Megestrol 40mg tablets will be distributed directly to site following confirmation that all necessary regulatory and ethical approvals are in place.

Further details on the ordering of supplies and dispensing procedures are provided in the pharmacy manual.

### **11.7.2 Dose, Route and Administration**

Patient will self-administer Megestrol 40mg by mouth. Patients in Arm B will take Megestrol 40mg tablets to be taken ONCE a day for 15 (+ ≤4) days prior to tumour excision. It can be taken with or without food.

If vomiting occurs shortly after the Megestrol tablet is swallowed, the dose should only be replaced if all of the intact tablet can be seen. Should any patient miss a scheduled dose for whatever reason (e.g. as a result of forgetting to take the tablets), the patient will be allowed to take the scheduled dose up to a maximum of 12 hours after that scheduled dose time. If greater than 12 hours after the scheduled dose time, the missed dose is not to be taken and the patient should take their next dose at the next scheduled time.

### **11.7.3 Storage conditions**

Megestrol 40mg tablets is stored at room temperature (25°C), excursions are permitted to 15-30°C, and kept in the original package in order to protect from moisture or as per instructions on the label.

### **11.7.4 Labelling**

Megestrol 40mg tablets will be provided to participating sites already labeled according to Eudralex Volume 4: Annex 13 Investigational Medicinal Products of the EU guide to GMP. Sample of the label can be found in the Pharmacy Manual.

### **11.7.5 Returns and destructions**

All previously dispensed, unused Megestrol acetate 40mg should be destroyed once the amount of remaining tablets has been counted and recorded in the relevant

[figure not shown]

accountability forms. Refer to the pharmacy manual.

#### 11.7.6 Adverse Events (AEs)

The most common Adverse Events (AEs):

Weight gain, thromboembolic phenomena, glucocorticoid effects, heart failure, nausea and vomiting, edema, breakthrough menstrual bleeding, dyspnea, tumor flare (with or without hypercalcemia), hyperglycemia, glucose intolerance, alopecia, hypertension, carpal tunnel syndrome, mood changes, hot flashes, malaise, asthenia, lethargy, sweating and rash.

See the current SIMPD for complete list of adverse effects.

#### 11.7.7 Contraindications

History of hypersensitivity to Megestrol acetate or any component of the formulation.

### **11.8 Megestrol acetate 160mg tablets**

#### 11.8.1 Legal status

Megestrol acetate 160mg daily is currently licenced in the UK for the treatment of hormone-dependant breast cancer.

Description: Megestrol acetate is a potent progestogen that exerts significant anti-oestrogenic effects. It has no androgenic or oestrogenic properties. It has anti-gonadotropic, anti-uterotropic and anti-androgenic/anti-myotropic actions. It has a slight but significant glucocorticoid effect and a very slight mineralocorticoid effect.

Supply: Commercial Megestrol 160mg tablets will be obtained locally by the investigating sites in keeping with standard local practice. Its handling and management will be subject to standard procedures of the pharmacy.

#### 11.8.2 Dose and Route and Administration

Patient will self-administer Megestrol by mouth. Patients in Arm C will take Megestrol 160mg tablets to be taken ONCE a day for 15 (+  $\leq 4$ ) days prior to tumour excision. It can be taken with or without food. There is no specific brand of Megestrol 160mg that must be used for this trial. Sites must ensure that the active substance used is Megestrol Acetate.

If vomiting occurs shortly after the Megestrol tablet is swallowed, the dose should only be replaced if all of the intact tablet can be seen. Should any patient miss a scheduled dose for whatever reason (e.g. as a result of forgetting to take the tablets), the patient will be allowed to take the scheduled dose up to a maximum of 12 hours after that scheduled dose time. If greater than 12 hours after the scheduled dose time, the missed dose is not to be taken and the patient should take their next dose at the next scheduled time.

#### 11.8.3 Storage conditions

Megestrol 160mg must be stored, handled and dispensed as detailed in the current SmPC of the brand being used. Megestrol 160mg is stored at room temperature below

[figure not shown]

25°C, and kept in the original package in order to protect from moisture or as per SmPC for the brand used.

#### 11.8.4 Labelling

Megestrol 160mg tablets will be labeled according to Eudralex Volume 4: Annex 13 Investigational Medicinal Products of the EU guide to GMP at the participating sites. An example of the label can be found in the Pharmacy Manual.

#### 11.8.5 Returns and destructions

All previously dispensed, unused Megestrol acetate 160mg should be destroyed once the amount of remaining tablets has been counted and recorded in the relevant accountability forms. Refer to the pharmacy manual for further details.

#### 11.8.6 Adverse Events (AEs)

The most common Adverse Events (AEs):

Weight gain, thromboembolic phenomena, glucocorticoid effects, heart failure, nausea and vomiting, edema, breakthrough menstrual bleeding, dyspnoea, tumor flare (with or without hypercalcemia), hyperglycemia, glucose intolerance, alopecia, hypertension, carpal tunnel syndrome, mood changes, hot flashes, malaise, asthenia, lethargy, sweating and rash. See package insert for complete list of adverse effects and the current SmPC for the brand being used.

#### 11.8.7 Contraindications

History of hypersensitivity to Megestrol acetate or any component of the formulation.

### **11.9 IMP delivery**

In the event of local guidance advising that hospital visits should be avoided or the participant is unable to collect the medication in person, the trial treatment can be delivered directly to the participant's home from the site by courier. Please see the Pharmacy Manual for more information.

### **11.10 Dosage modifications**

There will be no dose reductions for Letrozole or Megestrol acetate. Letrozole +/- Megestrol acetate may be held or discontinued at the discretion of the treating physician for endocrine-related toxicity, however patients will be excluded from the final analysis if they do not complete at least 13 days of the full 15 day pre-operative window dosing schedule (or  $\geq 80\%$  days of dosing if 16 to 19 days of treatment).

### **11.11 Concomitant therapy**

Treatment with concomitant, systemic or investigational anti-cancer agents are not allowed in this trial.

Avoid Co-administration of Letrozole with Tamoxifen, other anti-oestrogens or oestrogen-containing therapies as these substances may diminish the pharmacological action of Letrozole.

Supportive care, including but not limited to anti-emetic medications, may be administered at the discretion of the site PI, as medically indicated.

All concomitant medication must be recorded on the CRF. Standard intra- and peri-operative medications routinely administered at the study site, including anesthesia,

[figure not shown]

prophylactic antibiotics and anticoagulants, should not be recorded on the CRF. However, these medications should be recorded on the CRF if considered medically relevant by the PI.

## **12 Assessment of Safety**

### **12.1 Definitions**

#### **12.1.1 Adverse Event (AE)**

Any untoward medical occurrence in a patient or clinical trial subject administered a medicinal product and which does not necessarily have a causal relationship with this treatment.

An AE can therefore be any unfavourable and unintended sign (including an abnormal laboratory finding), symptom, or disease temporally associated with the use of an investigational medicinal product, whether or not considered related to the investigational medicinal product.

Please note: Recording of all AEs must start from the point of IC regardless of whether a patient has yet received a medicinal product.

#### **12.1.2 Adverse Reaction to an investigational medicinal product (AR)**

All untoward and unintended responses to an investigational medicinal product related to any dose administered. All AEs judged by either the reporting investigator or the sponsor as having a reasonable causal relationship to a medicinal product qualify as Adverse Reactions (ARs). The expression reasonable causal relationship means to convey in general that there is evidence or argument to suggest a causal relationship.

#### **12.1.3 Unexpected adverse reaction**

An Adverse Reaction (AR), the nature or severity of which is not consistent with the applicable Reference Safety Information (RSI), as evident from the SmPC or SIMPD.

When the outcome of the AR is not consistent with the applicable RSI this AR should be considered as unexpected.

The term "severe" is often used to describe the intensity (severity) of a specific event. This is not the same as "serious," which is based on patient/event outcome or action criteria.

#### **12.1.4 Serious Adverse Event or Serious Adverse Reaction (SAE / SAR)**

Any untoward medical occurrence that at any dose:

- results in death
- is life-threatening
- requires hospitalisation or prolongation of existing inpatients hospitalisation,
- results in persistent or significant disability or incapacity
- is a congenital anomaly or birth defect.
- is an important medical event - Some medical events may jeopardise the patient or may require an intervention to prevent one of the above characteristics/consequences. Such events (hereinafter referred to as 'important medical events') should also be considered as 'serious'.

[figure not shown]

Life-threatening in the definition of a SAE or SAR refers to an event in which the patient was at risk of death at the time of event; it does not refer to an event which hypothetically might have caused death if it were more severe.

#### **12.1.5 Suspected Unexpected Serious Adverse Reaction (SUSAR)**

A Serious Adverse Reaction (SAR), the nature and severity of which is not consistent with the information set out in the RSI.

#### **12.1.6 Reference Safety Information (RSI)**

A list of medical events that defines which reactions are expected for the IMP within a given trial and thus determining which SARs require expedited reporting.

The Reference Safety Information (RSI) approved by Medicines and Healthcare products Regulatory Agency (MHRA) for use in this trial is:

- Letrozole: Table 1 of section 4.8 of SmPC for Letrozole 2.5mg film-coated tablets (Accord)
- Megestrol acetate (40mg): "Adverse Reactions" section of sIMPD for Megestrol acetate tablet Par Pharmaceutical Inc.
- Megestrol acetate (160mg): Table in section 4.8 of the SmPC Megace 160 mg tablets (Bausch & Lomb U.K Limited).

### **12.2 Expected Adverse Reactions/Serious Adverse Reactions (AR /SARs)**

All expected ARs are listed in the latest MHRA approved version of the reference safety information as specified in section 12.1.6. This must be used when making a determination as to the expectedness of the AR. If the AR meets the criteria for seriousness, this must be reported as per section 12.6.

### **12.3 Expected Adverse Events/Serious Adverse Events (AE/SAE)**

All AEs/SAEs should be recorded in the trial documentation and CRF excepting minor side effects of the biopsy such as grade 1 bleeding, bruising or pain, as well as skin reactions to the plaster following biopsy or phlebotomy.

Hospitalisation for scheduled breast tumour excision should not be treated as an AE and as such should not be recorded or reported.

All AEs/SAEs should be recorded in the trial documentation and CRF excepting minor side effects related to standard tumour excision and unrelated to the study drug. These include grade  $\leq 2$ :

- Bleeding
- Pain
- Bruising
- Infection
- Post-Op Drain Complications

Any incidence of thromboembolism, however, will need to be recorded and reported if the event fulfills the criteria for seriousness as per section 12.1.4.

[figure not shown]

#### **12.4 Evaluation of adverse events**

The Sponsor expects that AEs are recorded from the point of IC regardless of whether a patient has yet received a medicinal product. Individual AEs should be evaluated by the investigator. This includes the evaluation of its seriousness and any relationship between IMP(s) and/or concomitant therapy and the AE (causality).

##### 12.4.1 Assessment of seriousness

Seriousness is assessed against the criteria in section 12.1.4. This defines whether the event is an AE, SAE or a SAR.

##### 12.4.2 Assessment of causality

Definitely: A causal relationship is clinically/biologically certain. **This is therefore an Adverse Reaction**

Probable: A causal relationship is clinically / biologically highly plausible and there is a plausible time sequence between onset of the AE and administration of the investigational medicinal product and there is a reasonable response on withdrawal. **This is therefore an Adverse Reaction.**

Possible: A causal relationship is clinically / biologically plausible and there is a plausible time sequence between onset of the AE and administration of the investigational medicinal product. **This is therefore an Adverse Reaction.**

Unlikely: A causal relation is improbable and another documented cause of the AE is most plausible. **This is therefore an Adverse Event.**

Unrelated: A causal relationship can be definitely excluded and another documented cause of the AE is most plausible. **This is therefore an Adverse Event.**

Unlikely and Unrelated causalities are considered NOT to be trial drug related

Definitely, Probable and Possible causalities are considered to be trial drug related

A pre-existing condition must not be recorded as an AE or reported as an SAE unless the condition worsens during the trial and meets the criteria for reporting or recording in the appropriate section of the CRF.

##### 12.4.3 Clinical assessment of severity

All Adverse Events (AEs) should be graded for severity according to the NCI-CTCAE Toxicity Criteria (Version 4.03). CTCAE v4.03 can be downloaded from the following URL:

[http://evs.nci.nih.gov/ftp1/CTCAE/CTCAE\\_4.03\\_2010-06-14\\_QuickReference\\_8.5x11.pdf](http://evs.nci.nih.gov/ftp1/CTCAE/CTCAE_4.03_2010-06-14_QuickReference_8.5x11.pdf)

##### 12.4.4 Recording of adverse events

Adverse Events (AEs) and Adverse Reactions (ARs) should be recorded in the medical notes and the appropriate section of the CRF and/or AE/AR log. SAEs and SARs should be reported to the sponsor as detailed in section 12.5.

#### **12.5 Reporting serious adverse events**

Each Principal Investigator needs to record all AEs and report SAEs to the Chief Investigator (CI) using the trial specific SAE form within 24 hours of their awareness of the event. The CI is responsible for ensuring the assessment of all SAEs for

[figure not shown]

expectedness and relatedness is completed and the onward notification of all SAEs to the Sponsor immediately but not more than 24 hours of first notification. The sponsor has to keep detailed records of all SAEs reported to them by the trial team.

The Chief Investigator (CI) is also responsible for prompt reporting of all SAE findings to the competent authority (e.g. MHRA) of each concerned Member State if they could:

- adversely affect the health of patients
- impact on the conduct of the trial
- alter the risk to benefit ratio of the trial
- alter the competent authority's authorisation to continue the trial in accordance with Directive 2001/20/EC.

The completed SAE form can be faxed or emailed. Details of where to report the SAE's can be found on the PIONEER SAE form and the front cover of the protocol.

SAE/SARs should be recorded and reported up to the post-treatment follow-up visit and any SAEs will be followed up until resolved to grade 1.

## **12.6 Reporting of Suspected Unexpected Serious Adverse Reactions (SUSARs)**

All suspected adverse reactions related to an investigational medicinal product (the tested IMP and comparators) which occur in the concerned trial, and that are both unexpected and serious (SUSARs) are subject to expedited reporting. Please see section 12.1.6 for the Reference Safety Information to be used in this trial.

### 12.6.1 Who should report and whom to report to?

The Sponsor delegates the responsibility of notification of SUSARs to the CI. The CI must report all the relevant safety information previously described, to the:

- Sponsor
- competent authorities in the concerned member states (e.g. MHRA)
- Ethics Committee in the concerned member states

The CI shall inform all investigators concerned of relevant information about SUSARs that could adversely affect the safety of patients.

### 12.6.2 When to report?

#### 12.6.2.1 Fatal or life-threatening SUSARs

All parties listed in 12.6.1 must be notified as soon as possible but no later than **7 calendar days** after the trial team and Sponsor has first knowledge of the minimum criteria for expedited reporting.

In each case relevant follow-up information should be sought and a report completed as soon as possible. It should be communicated to all parties within an additional **8 calendar days**.

#### 12.6.2.2 Non-fatal and non-life-threatening SUSARs

All other SUSARs and safety issues must be reported to all parties listed in 12.6.1 as soon as possible but no later than **15 calendar days** after first knowledge of the minimum criteria for expedited reporting. Further relevant follow-up information should be given as soon as possible.

[figure not shown]

### 12.6.3 How to report?

#### 12.6.3.1 Minimum criteria for initial expedited reporting of SUSARs

Information on the final description and evaluation of an AR report may not be available within the required time frames for reporting. For regulatory purposes, initial expedited reports should be submitted within the time limits as soon as the minimum following criteria are met:

- a) a suspected investigational medicinal product,
- b) an identifiable patient (e.g. trial patient code number),
- c) an adverse event assessed as serious and unexpected, and for which there is a reasonable suspected causal relationship,
- d) an identifiable reporting source,

and, when available and applicable:

- an unique clinical trial identification (EudraCT number or in case of non-European Community trials the sponsor's trial protocol code number)
- an unique case identification (i.e. sponsor's case identification number).

#### 12.6.3.2 Follow-up reports of SUSARs

In case of incomplete information at the time of initial reporting, all the appropriate information for an adequate analysis of causality should be actively sought from the reporter or other available sources. Further available relevant information should be reported as follow-up reports.

In certain cases, it may be appropriate to conduct follow-up of the long-term outcome of a particular reaction.

#### 12.6.3.3 Format of the SUSARs reports

Electronic reporting is the expected method for expedited reporting of SUSARs to the competent authority. The format and content as defined by the competent authority should be adhered to.

## **13 Evaluation of Results (Definitions and response/evaluation of outcome measures)**

### **13.1 Trial Outcome Measures**

#### 13.1.1 Primary efficacy outcome measure

Change in tumour proliferation measured by Ki67 immuno-histochemical assessment (%) at baseline compared to Day 15 (+  $\leq 4$  days).

Ki67 expression will be measured centrally, blinded with treatment allocation, using formalin-fixed, paraffin embedded histopathology sections of the tumour tissue specimens taken at baseline and at Day 15 (+  $\leq 4$ ) days. Additional analyses will also be done on the tumour biopsy specimens taken at breast tumour excision (or the additional research biopsy if tumour excision is not performed on Day 15 +  $\leq 4$  days). IHC for the Ki67-proliferation associated antigen will be carried out on 3-4  $\mu\text{m}$  sections of the routinely processed material following heat mediated antigen retrieval and with the appropriate primary antibodies.

The tumour-cell Ki67 antigen labeling index will be recorded following the

[figure not shown]

recommendations from the International Ki67 working group [19]. Sections from the diagnostic or baseline core biopsy, Day 15 (+  $\leq 4$ ) tumour biopsy/post-surgical specimen will be stained for Ki67. Tumour cell nuclei showing any intensity of staining will be regarded as positive. The stained slide will be reviewed at low power and representative high power fields (x40) will be selected for counting; if there are clear areas with an increased proportion of cells staining (hot spots) these will be included in the count. One thousand tumour cell nuclei will be counted; if there are less than 1000 tumour cells in a biopsy a minimum of 500 will be counted. If there are less than 500 cell nuclei then further sections will be stained at a depth of 25 $\mu$ m and counted until the minimum number of cells is reached. Ki67 will be scored as the percentage of tumour nuclei staining. The investigators analyzing Ki67 will be blinded as to treatment allocation. Ki67-response is defined as a 50% or higher fall in Ki67 expression.

### 13.1.2 Secondary outcome measure

Secondary endpoints:

- Change in tumour apoptosis, measured by Caspase 3 (IHC) between baseline and Day 15 (+ $\leq 4$  Days)  
Caspase-3 is synthesized as an inactive proenzyme which is activated by cleavage in cells undergoing apoptosis. Apoptotic cells can be detected more easily by IHC with an antibody for activated (cleaved) caspase-3. Caspase-3 IHC has been validated as a marker of apoptosis in breast cancer [20]
- Change in expression of Androgen Receptor and PR by IHC between baseline and Day 15 (+ $\leq 4$  Days)  
IHC of PR will be performed as a surrogate of ER activity, and to correlate Ki67 changes to PR levels. Like PR, Androgen Receptor influences ER- $\alpha$  activity in breast cancer, and has been shown to be a predictor of response to medroxyprogesterone acetate (a synthetic progestin) in breast cancer. We will correlate Ki67 changes to Androgen Receptor levels.
- Change in proliferation by Aurora Kinase A labeling by IHC between baseline and Day 15 (+ $\leq 4$  Days)  
In a series of 3093 women with breast cancer, Aurora Kinase A by IHC was found to outperform other proliferation markers as an independent predictor of breast cancer specific survival in ER-positive breast cancer [21]. Given that Ki67 remains the current accepted proliferative marker, however, Aurora Kinase A will be analysed alongside
- Absolute value of Ki67 at day 15 (+ $\leq 4$  Days)  
This is included as a secondary endpoint with a view to inform the development of a larger adjuvant trial following PIONEER. The absolute value of Ki67 at Day 15 has been found to be better predictive of recurrence free survival [16, 17]

Secondary safety endpoints:

- incidence of SAEs
- incidence of AEs of all grades (CTCAE V4.03)

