## **7 Rationale for Trial**

### **7.1 Data from non-clinical trials**

It has been known for many years that Oestrogen receptor (ER) directly induces expression of the Progesterone Receptor (PR) in normal and malignant breast epithelial cells, so that these steroid receptors commonly co-localise. Historically, the accepted explanation was that PR-positivity was a passive consequence of a functional ER, and PR was established as a biomarker of ER functionality in breast cancer [4]. However in recent years, the [name] laboratory (Cambridge Institute, Cancer Research UK) has published preclinical findings exploring ERfunction in breast cancer, providing new insights into progestogen action and functional 'cross-talk' between ER and PR in breast cancer [5].

These preclinical discoveries have provided an alternative explanation to the previous over-simplistic assumption that PR is just a passive consequence of an active ER. In fact, PR can be the cause and not the consequence of altered ER activity.

In the presence of agonist ligands, progesterone-activated PR causes rapid redistribution or sequestration of  $ER\alpha$  chromatin binding sites in breast cancer cells, resulting in a unique gene expression program that is associated with a good clinical outcome, via inhibition of  $ER\alpha$ -mediated transcriptional activity and the oestrogen-mediated proliferative response (Figure 2). Thus, PR functions as a molecular rheostat to control  $ER\alpha$  chromatin binding and transcriptional activity, with important implications for prognosis and therapeutic interventions.

This functional 'cross-talk' between  $ER\alpha$  and PR was explored preclinically by the demonstration that progesterone inhibited oestrogen-mediated growth in primary  $ER\alpha$ + breast tumour explants and  $ER\alpha$ + cell line xenografts [5]. In both MCF-7 and T-47D xenograft models, progesterone alone antagonized oestrogen-induced tumour

[figure not shown]

formation, as did tamoxifen alone. However, the combination of tamoxifen and progesterone had the greatest tumour inhibitory effect.

The potential clinical significance of exploiting this interaction between ER and PR signaling in breast cancer affords the possibility that the addition of a progesterone agonist might enhance the anti-proliferative effect of anti-oestrogen therapies and therefore prove a more effective combination therapy.

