### **8.6.2 Secondary endpoints:**

#### **Biological Endpoints**

- Change in tumour apoptosis between baseline and Day 15 (+/-4 Days), measured by Caspase 3 (IHC)
- Change in expression of androgen receptor and PR (IHC) between baseline and Day 15 (+/-4 Days)
- Change in proliferation by Aurora Kinase A (IHC) between baseline and Day 15 (+/-4 Days)
- Absolute value of Ki67 at Day 15 (+/-4 Days)

[figure not shown]**Safety Endpoints**

- Incidence of Serious Adverse Events (SAEs)
- Incidence of Adverse Events (AEs) of all grades (CTCAE Version 4.03)

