## **14 Statistics**

### **14.1 Statistical methods**

The primary outcome measure is the change in tumour proliferation measured by Ki-67 immuno-histochemical (IHC) assessment (%) at baseline and on day 15 (+  $\leq$ 4 days). The standard t-test will be applied for the primary comparison between Arm A vs Arm (B+C) based on evaluable patients.

The primary analysis for the primary endpoint will be based on the evaluable population (defined as eligible patients who have completed at least 13 [or 80%] of the full 15 Day [+  $\leq$ 4 Days] dosing schedule).

Adverse events will be summarized for the safety population (defined as all patients who have received at least one dose of protocol treatment) using frequency tables and compared using the Wilcoxon Mann-Whitney test or Kruskal Wallis test. All other secondary outcomes will be summarised using the summary statistics and compared between arms using t-test, ANOVA, Wilcoxon Mann-Whitney test or Kruskal Wallis test where ever is appropriate. A comprehensive statistical-analysis plan will be prepared before any analysis is performed.

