### **14.2 Number of Subjects to be enrolled**

In this open-label, three-arm, randomized, phase II trial; patients will be randomised in a ratio 1(A):1.5(B):1.5(C) in favour of the 2 combination arms of Letrozole + Megestrol acetate. Our hypothesis is that the addition of Megestrol acetate increases the anti-proliferative effect of Letrozole when given for 2 weeks pre-operatively in patients with early-stage, ER-positive breast cancer, as measured by Ki-67.

Based on the results from the *Opportune* study [23], where a significantly greater geometric mean Ki-67 suppression of 83.8% (one-sided 95% CI,  $\geq$  79.0%) was reported for the combination arm, and 66.0% (95% CI,  $\leq$ 75.4%) for anastrozole alone

[figure not shown]

arm (geometric mean ratio [combination: anastrozole], 0.48; 95% CI,  $\leq 0.72$ ;  $P = .004$ ), this translates to the estimated standard deviation is 0.242. We therefore have assumed a mean 66% reduction in Ki67 for the Letrozole alone arm of PIONEER (Arm A). It is anticipated that there is a mean 77.5% reduction in Ki67 in arms B and C for all patients (approximately one third PR negative, and two thirds PR positive), and a mean 80.0% reduction in Ki67 in arms B and C for patients with PR positive, which was based on the anti-proliferative effect seen in preclinical models [5]. Enrichment design is applied with the overall significance level of 5% (one-sided) ( $5\% (\alpha) = 2.5\% (\alpha_{all}) + 2.5\% (\alpha_{PR+})$ ) and a power of 80%, and common standard deviation of 0.242, using the two-sample t-test comparing Arm A vs. Arm (B+C):

- all patients

a total of 189 patients (Arm A  $n=47$ , Arm B  $n=71$ , Arm C  $n=71$ ) is needed to detect the mean reduction in Ki67 of 66% in Arm A to 77.5% in Arm (B+C);

- patients with PR positive breast cancer

a total of 149 PR positive patients (Arm A  $n=37$ , Arm B  $n=56$ , Arm C  $n=56$ ) is needed to detect the mean reduction in Ki67 of 66% in Arm A to 80.0% in Arm (B+C);

The total number of evaluable patients required is 189 with 149 PR positive. It is anticipated that this will require approximately 10% more patients to be randomised, to account for patients that may not be evaluable.

It is therefore planned to randomise approximately 210 patients with 166 PR positive ( $210 \times 90\% = 189$ ,  $166 \times 90\% = 149$ ).

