### **14.3 Enriched data monitoring**

The patient population will be monitored (PR positive vs. PR negative) regularly during patient recruitment in order to achieve the required sample size for patients with PR positive. This will be regularly reviewed by the Independent Data Monitoring Committee (IDMC) and the recruitment plan will be amended accordingly if needed.

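### Change in PR is compared between arms without regard to baseline PR, although 21% to one third of patients will be PR negative and have little or no PR to lose

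*Protocol*

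**What the plan says.** - **Endpoint.** Protocol 8.6.2 lists "Change in expression of androgen receptor and PR (IHC) between baseline and Day 15" among the secondary biological endpoints, with no restriction by baseline PR. The inclusion criteria (9.1) require ER positivity and set no PR requirement.
- **Purpose.** 13.1.2: "IHC of PR will be performed as a surrogate of ER activity, and to correlate Ki67 changes to PR levels". Section 7.1 supplies the biology: ER "directly induces expression of the Progesterone Receptor (PR) in normal and malignant breast epithelial cells".
- **Analysis.** 14.1: "All other secondary outcomes will be summarised using the summary statistics and compared between arms using t-test". The sentence goes on to allow ANOVA and two rank tests, as appropriate. No population is named for this endpoint and no listed test uses baseline PR. A fuller statistical analysis plan is promised.
- **PR mix.** 14.2 bases the all-patient Ki67 effect on a population that is "approximately one third PR negative, and two thirds PR positive", and then sets the target: "The total number of evaluable patients required is 189 with 149 PR positive". Section 14.3 monitors recruitment by PR status "in order to achieve the required sample size for patients with PR positive".

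**The concern.** If ER induces PR, and PR is read as a surrogate of ER activity, then a treatment that lowers ER activity should show as a fall in PR. A tumour that starts with little or no PR cannot show that fall in any arm. Including such tumours in an unadjusted comparison pulls the mean arm difference towards zero. It also mixes near-zero changes with real falls, which widens the spread relative to the remaining difference.

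At stake is the secondary endpoint that reads out ER signalling by IHC. A real difference would be more likely to be missed, and the reported average would be smaller than the effect in tumours able to respond. The protocol already treats PR status as important for Ki67, with its own hypothesis, alpha share and recruitment target, but does not carry that through to the endpoint that is PR itself.

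**Working it through.** **1. The plan's own figure.** No sample size or power is stated for PR change, so the check borrows the arm sizes of the primary comparison. Those reproduce. With a Ki67 difference of 0.115, SD 0.242, one-sided 2.5%, 80% power and a 1:3 split (A against B+C), the number in Arm A is (1.960 + 0.842)² × 0.242² × (1 + 1/3) / 0.115² = 46.3, so 47. The total is 188, against 189 stated (47 and 142). Exact t-test power at 47 against 142 is 80.2%.

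**2. PR-negative share.**
- From the target: (189 − 149)/189 = 40/189 = 21.2%.
- From the effect-size assumption: one third, so 126 of 189 PR positive.

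These two figures in 14.2 differ. The recruitment target is the lower share, so both are carried.

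**3. Dilution of the mean.** Let f be the PR-positive share and d the arm difference in PR-positive patients. Assume the change in PR-negative patients is 0 in every arm. The all-patient difference is then f × d:
- f = 149/189: 0.79 d
- f = 2/3: 0.67 d

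**4. Power (illustrative).** The protocol gives no PR mean or SD, so everything is in units of the SD within PR-positive patients. Let m be an arm's mean fall there. Its all-patient variance is f + f(1 − f)m², with m in the control arm and m + d in the combined arms, pooled over 47 and 142. Power is from the noncentral t distribution, two-sided 5%. The PR-positive comparison uses n = 149 or 126, split 1:3, with SD 1.

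For d = 0.5 and a control fall of 1:

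| PR positive | All-patient difference | All-patient SD | Noncentrality, all 189 | Power, all 189 | Noncentrality, PR positive only | Power, PR positive only |
|---|---|---|---|---|---|---|
| 149 | 0.394 | 1.055 | 0.394/1.055 × √(47×142/189) = 2.22 | 60% | 0.5 × √(149×3/16) = 2.64 | 75% |
| 126 | 0.333 | 1.048 | 0.333/1.048 × √(47×142/189) = 1.89 | 47% | 0.5 × √(126×3/16) = 2.43 | 67% |

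**5. Range.** Loss in points against the PR-positive comparison, for d from 0.4 to 0.6:

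| Control fall (SD) | 149 PR positive | 126 PR positive |
|---|---|---|
| 0 | 1 to 2 | 1 to 3 |
| 0.5 | 5 to 7 | 7 to 11 |
| 1 | 12 to 15 | 15 to 23 |
| 1.5 | 19 to 24 | 22 to 34 |

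The all-patient comparison is never better on this grid, despite its larger n.

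**6. Do the alternatives in 14.1 help?** In simulation under the assumptions of step 4, Mann-Whitney power in all patients was 56% (149) and 39% (126), against 74% and 64% in PR-positive patients, so the rank test does not recover the loss. An all-patient model adjusted for baseline PR status does: 74% and 66%, about the same as restriction.

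**The case against.** The strongest reply is that the protocol fixes little here. It names no population for this endpoint, leaves the choice of test open and promises an analysis plan. Population and baseline adjustment for one secondary IHC marker are ordinary content for that plan. This stands in part: a reader might infer that the protocol commits to an unadjusted t-test over all patients, and it does not say so. What remains is that it defines the endpoint, its purpose and a list of tests, and neither the definition nor any listed test accounts for baseline PR.

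Other parts of the reply also stand:
- The protocol speaks of change, never of a fall. The fall is inferred from 13.1.2 and 7.1, and a floor blocks only decreases.
- No PR cut-off or scale is given. That PR-negative tumours sit near zero and stay there is reasoned, not documented. A cut-off that counts low PR as negative would soften the effect.
- The size of the loss depends mostly on the assumed control fall. At 0 SD it is 1 to 3 points.
- The all-patient mean difference is a valid average for the enrolled population. It is diluted as a reading of ER activity, but not biased.
- PR status is not a minimisation factor, but chance imbalance in it is already contained in the mixture variance of step 4 and is not a further loss.
- ChIP-seq and RNA sequencing address the mechanism separately, as exploratory endpoints.

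**Conclusion.** The point holds as a modest one about a secondary endpoint. Given the stated purpose, a comparison that ignores baseline PR is a weaker choice than one that uses it, and the better choice costs almost nothing. If PR-negative change is about 0, the mean arm difference is multiplied by 0.79 (21% PR negative) to 0.67 (one third). The loss of power lies between about 1 and 34 points over the assumed range and cannot be narrowed from the protocol.

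Two stronger readings are not supported. A reader might take one third PR negative as the planned mix. That figure is the effect-size assumption, and the monitored target implies 21%. A reader might also take a loss of 15 to 20 points as established. It follows from assuming a 0.5 SD difference and a 1 SD control fall, neither of which the protocol gives. Nothing here touches the primary Ki67 analysis, which has its own PR-positive test.

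**What to change.** Add one sentence to 13.1.2 and 14.1: the main between-arm comparison of change in PR is made in patients PR positive at baseline or, equivalently for power, in all patients with adjustment for or stratification by baseline PR status. Report PR-negative patients descriptively, including the number in whom PR appears at Day 15.

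This needs no new data, since PR status is already tracked for recruitment under 14.3. The small downside is that PR induction in PR-negative tumours is described rather than tested.
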